## Abstract

**Background:**

Patients with cervical spondylosis myelopathy (CSM) and complicated with hypertension are often experiencing a blood pressure decrease after taking cervical decompressive surgery in clinical observations, but how this blood pressure reduction is associated with the surgery, which cut cervical sympathetic nervous, has never been rigorously assessed. Thus, the purpose of this study is to investigate the effect of cervical decompressive surgery on blood pressure among CSM patients with hypertension.

**Methods/Design:**

The study will be a time series cohort study. Fifty eligible patients will be selected consecutively from the Peking University First Hospital. Two 24-h ambulatory blood pressure measurement (ABPM) will be taken before the surgery, apart by at least 3 days. The patients will be followed up for another two ABPMs at 1 and 3 months after the surgery.

We will recruit subjects with cervical spondylosis myelopathy meeting operation indications and scheduled for receiving cervical decompressive surgery, aged 18–84 years, have a history of hypertension or office systolic blood pressure ≥140 mmHg on initial screening, and willing to participate in the study and provide informed consent. Exclusion criteria includes a history of known secondary hypertension, visual analogue scale (VAS) score ≥4, and unable to comply with study due to severe psychosis.

The change in systolic ABPs over the four times will be analyzed to observe the overall pattern of the blood pressure change in relation to the surgery, but the primary analysis will be the comparison of systolic ABP between the 2^nd^ and 3^rd^ , 4^th^ measurements (before and after the surgery). We will also calculate the regression-to-the-mean adjusted changes in systolic ABP as sensitivity analysis. Secondary endpoints are the changes in 24 h ABPM diastolic blood pressure, blood pressure control status, the use and dose adjustment of antihypertensive medication, and the incidence of operative complications. Primary outcome analyses will be carried out using analysis of covariance, as well as the first secondary endpoint.

**Discussion:**

This study will inform us the important knowledge about cervical sympathetic nervous system (SNS) and blood pressure. Once confirmed, it may help to produce new method for control of hypertension, which is the leading cause of death in the world.

**Trial registration:**

The study is registered to Clinical Trials.gov (NCT02016768).

## Background

Hypertension is a major global health concern. It is estimated that 30–40 % of the adult population in the developed world are suffering from hypertension [1, 2]. Moreover, incidence and prevalence of hypertension are increasing, especially in developing countries. The effects of current pharmacologic treatment of hypertension remain suboptimal in both developing and developed countries [3, 4]. The common causes responsible for the poor control of high blood pressure are attributed to physicians’ attitudes and patient non-compliance to lifelong pharmacological therapy for asymptomatic hypertension [5–7]. Moreover, hypertension that remains uncontrolled in spite of the use of 3 or more antihypertensive drugs has been called resistant hypertension [8]. Clinical evidence indicates that the risk of major cardiovascular events is higher among patients with resistant hypertension than that among patients with controlled blood pressure [5]. Thus, developing novel approaches for management of hypertension, especially for resistant hypertension, is an important issue for the future of the treatment of hypertension.

It is well known that sympathetic nerve fibers are rich in cervical spinal tissues [9–11]. Yamada et al. [9] reported that there was different sympathetic innervation between the cervical dura mater and the posterior longitudinal ligament. It seems reasonable that the compression or irritation of cervical dura mater and/or posterior longitudinal ligament may cause an increase in blood pressure or aggravate pre-existing hypertension among patients with cervical spondylosis myelopathy.

Tamura [12] found that neck injury, such as whiplash, may lead to the cranial symptoms of the Barré-Lieou syndrome (including a group of symptoms such as headache, vertigo, tinnitus and ocular problems), which may result from irritation of the sympathetic nervous supply. We hypothesize that the cervical sympathetic nerve is also associated with the occurrence of resistant hypertension and that cervical decompressive surgery may be beneficial in blood pressure control among patients with cervical spondylosis myelopathy [13]. The purpose of this study is to investigate the effect of cervical decompressive surgery on resistant hypertension based on a novel mechanistic hypothesis of essential hypertension.

## Methods and design

### Study design and Setting

The study is a time series cohort study. Patients with both cervical spondylosis myelopathy and hypertension are invited to participate in the study and subsequently receive cervical decompressive surgery. Patients are recruited continuously by surgeons at the Department of Orthopaedics, Peking University First Hospital in which there are about 30–40 patients with both cervical spondylosis myelopathy and hypertension each year. These subjects will be followed up at 1 and 3 months post-operation after enrollment. The study procedures and informed consent form have been approved by the Institutional Review Boards of the Peking University Health Science Center in Beijing, China, and registered at NCT02016768. Figure 1 shows an overview of the most important procedures in the study.

**Fig. 1 Fig1:**
[figure not shown]
Study measures and time points

### Participants

#### Inclusion criteria

The patients to be included in the study should meet the following inclusion criteria:Patients with cervical spondylosis myelopathy, such as bilateral hand clumsiness and numbness, walking unsteady, weakness in the limbs, muscular dystrophy, increasing deep tendon reflex and positive Hoffmann and Babinski signs; the underlying diseases including multilevel cervical spinal stenosis, ossification of posterior longitudinal ligaments (OPLL), disc herniation, meeting operation indications: spinal neurological symptoms for at least 2 months, which are not cured by conservative treatment or in progression, significant spinal compression indicated by magnetic resonance imaging.Aged 18–84 years.Plans for receiving cervical decompressive surgery.A history of hypertension or office systolic blood pressure ≥140 mmHg on initial screening.Willing to participate in the study and sign informed consent.

#### Exclusion criteria

If one of the following criteria is met, patients will be excluded from the study:A history of known secondary hypertension.Visual analogue scale (VAS) score ≥4.Unable to comply with study due to sever psychosis.

#### Recruitment and consent

The patients who suffer from cervical spondylosis myelopathy and plan for receiving cervical decompressive surgery will be selected for potential participation by the surgeons at the Department of Orthopedics. After consultation with inpatients and outpatients and screening their clinical information, the principal investigator of the study (the surgeon) informs patients whether they are eligible for the study. Informed consent is acquired immediately after screening for every subject by the principal investigator.

#### Withdrawal of individual subjects

Subjects can withdraw from the study at any time for any reason without any consequences. The investigator can also decide to release a subject from the study for medical reasons. For every subject who decides to withdraw from the study, the reasons for withdrawal will be recorded.

A total of 18 patients have given informed consent for participation and been enrolled into the study from July 2014 to Oct 2015.

### Cervical decompressive surgery

The cervical decompressive surgery will be done with one of the following four operating methods: international standard anterior cervical discectomy and fusion (standard Smith-Robinson technique, intervertebral disc incised and removed to reduce pressure, interbody fusion by implanting cervical interbody fusion cage), anterior cervical corpectomy and fusion (cervical corpectomy decompression, interbody fusion by implanting titanium cage), posterior bilateral open-door decompression (modified Hemo anchored method) or one-side open door decompression (modified Hirobayashi anchored method). The indications for anterior approach are subjects with less than three levels disc herniation, while for posterior approach are those with multilevel cervical spinal stenosis and continuous or mixed OPLL.

### Initial screening, assessment and follow-up

After providing informed consent, potential participants will be asked standardized questions about their demographic characteristics and medical history (especially for the history of hypertension and antihypertensive therapy) at initial screening. In addition, office blood pressure, VAS score and 24 h ambulatory blood pressure measurement (ABPM) will also be measured and used for checking inclusion/exclusion criteria (Fig. 2).

**Fig. 2 Fig2:**
[figure not shown]
Observation, assessment, and follow-up schedule

Eligible participants will be hospitalized for surgical treatment, and a pre-operation visit and clinical evaluation will be done before surgery, including antihypertensive medication, vital signs, physical examination, laboratory testing, spinal nerve function score and 24 h ABPM (Fig. 2). It is required that there is at least 3 days apart between initial screening visit and pre-operation visit. As soon as the operation condition is met, these subjects will receive cervical decompressive surgery, and their operation notes and adverse events will be recorded in detail.

All subjects will be followed up at 1 and 3 months after surgical operation, with antihypertensive medication recording, measurement of office blood pressure, 24 h ABPM and adverse events assessment collected at each time. In addition, VAS, physical examination and spinal nerve function score will be measured and collected at 3 month follow-up.

Regular antihypertensive medication therapy will be continued during the entire study period, however, the investigator can adjust the antihypertensive medication if necessary, according to treatment needs of individual patients.

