### Study endpoints

The primary endpoint is estimated as the difference between systolic ABPM before surgery (2^nd^ measurement) and the systolic ABPM at 1 month and 3 month post-operation (3^rd^ and 4^th^ measurement).

Four secondary endpoints were defined as: 1) The difference between diastolic ABPM before surgery and ABPM diastolic blood pressure at 1 month and 3 month post-operation; 2) control status of blood pressure at 1 month and 3 month post-operation (blood pressure control is achieved if systolic/diastolic blood pressure <140/90 mm Hg, reducing systolic blood pressure by >20 mm Hg or reducing diastolic blood pressure >5 mm Hg); 3) the use and dose adjustment of antihypertensive medication; and 4) the incidence of operative complications, including spinal nerve trauma, incision infection and fluid, pneumonia and urinary system infection etc.

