### Statistical analysis

Analyses will be made using SAS statistical software (version 9.3) by researchers at the Peking University Clinical Research Institute. The change in systolic ABPMs over the four times will be analyzed to observe the overall pattern of the blood pressure change in relation to the surgery, but the primary analysis will be the comparison of systolic ABPM between the 2^nd^ and 3^rd^, 4^th^ measurements (before and after the surgery). We will also calculate the regression-to-the-mean adjusted changes in systolic ABPMs as sensitivity analysis. Primary endpoint analyses and the change in systolic ABPMs over the four times will be carried out using analysis of covariance, as well as the first secondary endpoint (the change of 24 h ABPM diastolic blood pressure). Descriptive statistics will be used to summarize control status of blood pressure, the use and dose adjustment of antihypertensive medication and the incidence of operative complications.

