## Discussion

The etiology and mechanism of essential hypertension remains unclear. Non-operative methods of essential hypertension treatment including antihypertensive pharmacologic drugs are still unsatisfactory [5, 8]. In the past several years, a new procedure named renal denervation had been shown to be safe and effective in controlling hypertension, supporting that the sympathetic nervous system (SNS) activity is critical in regulating blood pressure [6, 7]. Recently, we have proposed a novel hypothesis that cervical spondylotic myelopathy may be an important etiology of essential hypertension which has been termed as cervicogenic hypertension [13]. In our previous study, we found that the high blood pressure in 12 out of 30 (40 %) hypertensive patients was reduced to normal levels following the cervical decompressive surgery, which resulted in a termination of the antihypertensive medications. Furthermore, the high and unstable blood pressure in the other 15 patients became stabilized and was well controlled by antihypertensive drugs after cervical decompressive surgery [13]. Recently, Peng et al. reported two cases of cervical spondylosis with hypertension [15]. After anterior cervical discectomy and fusion, the blood pressure of both the two patients remain normal without hypertensive medications [15]. Also, we speculate that renal denervation only destructs the network of SNS, and that the diseased cervical SNS has a greater impact on initiating and increasing SNS activity, as it may be closer to central nervous system than the normal renal SNS.

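### Antihypertensive drugs may be adjusted during follow-up, but the primary systolic ABPM change has no analysis that accounts for drug changes, so surgery and medication effects are mixed

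*Protocol article*

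**What the plan says.** All references are to the Protocol article.

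- **Initial screening, assessment and follow-up.** "Regular antihypertensive medication therapy will be continued during the entire study period", but "the investigator can adjust the antihypertensive medication if necessary, according to treatment needs of individual patients". No criteria for adjustment are given. Medication is recorded at the pre-operation visit, and patients return at 1 and 3 months "with antihypertensive medication recording, measurement of office blood pressure, 24 h ABPM and adverse events assessment collected at each time".
- **Study endpoints.** "The primary endpoint is estimated as the difference between systolic ABPM before surgery" (the 2nd measurement) and the 1- and 3-month values. Nothing in the definition refers to drug changes. Use and dose adjustment of antihypertensives is a separate secondary endpoint.
- **Statistical analysis.** The primary endpoint analyses "will be carried out using analysis of covariance, as well as the first secondary endpoint"; covariates are not named. For the primary: "We will also calculate the regression-to-the-mean adjusted changes in systolic ABPMs as sensitivity analysis". For medication: "Descriptive statistics will be used to summarize control status of blood pressure, the use and dose adjustment of antihypertensive medication".
- **Study design and Setting.** A single cohort, measured before and after surgery, without a control arm.
- **Discussion.** In the sponsor's earlier series the pressure of 12 of 30 hypertensive patients (40%) became normal after surgery, "which resulted in a termination of the antihypertensive medications". A lower drug burden is presented as an expected benefit. The limitations name placebo effects, Hawthorne effects and regression to the mean, but not drug changes.

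**The concern.** The abstract states the aim as the effect of surgery on blood pressure. Drug changes respond to the very pressure being measured, so they are not random noise around that effect. A patient whose pressure falls after decompression and whose drugs are then cut may show little change in ABPM. A patient whose drugs are stepped up after the 2nd ABPM may show a fall that surgery did not cause. A concurrent control group under the same drug management would give some basis for separating the two; this design has none.

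The sponsor's own account makes drug reduction foreseeable. If the hypothesis is right, part of the benefit will appear as fewer drugs and will be lost from the primary endpoint. Reporting medication separately does not repair this. Two marginal summaries cannot show whether the patients whose ABPM fell were on less, the same or more treatment.

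**Working it through.** **Inputs from Sample size calculation:** difference 11 mm Hg, SD of change 15 mm Hg, two-sided alpha 0.01, power 90%, dropout 20%, total 50.

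**Step 1: the plan's own figure.** For a paired change, n = (SD × (z₀.₉₉₅ + z₀.₉₀) / difference)² = (15 × (2.576 + 1.282) / 11)² ≈ 27.7, so 28, or 28/0.8 = 35 with dropout. The exact t-test version gives 32, or 32/0.8 = 40 with dropout. The stated 50 is not reproduced; it errs on the large side, and this point does not depend on it. With 50 enrolled and 20% lost, 50 × 0.8 = 40 complete. Power at 11 mm Hg is then 96.9% (noncentral t, 39 df, noncentrality 11 × √40 / 15 = 4.64). That is the baseline below.

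**Step 2: assumptions not in the documents.** Each drug change shifts 24 h systolic pressure by b = 5 or 10 mm Hg. A share f of patients changes. The 11 mm Hg is read as the fall at constant medication. SD stays at 15. The 40% row for reductions borrows the share from the earlier series, for which no timing is given.

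**Step 3: drugs reduced, true fall 11 mm Hg.** Observed mean fall = 11 − f × b.

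| Share reduced | b (mm Hg) | Observed fall (mm Hg) | Power, n = 40 |
|---|---|---|---|
| 10% | 5 | 10.5 | 95% |
| 10% | 10 | 10.0 | 93% |
| 20% | 5 | 10.0 | 93% |
| 20% | 10 | 9.0 | 85% |
| 40% | 5 | 9.0 | 85% |
| 40% | 10 | 7.0 | 60% |

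**Step 4: drugs intensified, no surgical effect.** Apparent fall = f × b.

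| Share intensified | b (mm Hg) | Apparent fall (mm Hg) | Rejection (nominal 1%) |
|---|---|---|---|
| 20% | 5 | 1.0 | 1.6% |
| 20% | 10 | 2.0 | 3.9% |
| 40% | 5 | 2.0 | 3.9% |
| 40% | 10 | 4.0 | 16.8% |

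**Step 5: robustness.** The shift in the mean, f × b, does not depend on which patients change drugs; the SD does. If changes are unrelated to the underlying fall, SD becomes √(15² + f(1 − f)b²). In the worst row of Step 3 that is √(225 + 24) ≈ 15.8, and power is 54% instead of 60%. In the worst row of Step 4 rejection is 14.9% instead of 16.8%. Reductions and intensifications in the same cohort partly cancel in the mean, so a small net shift would not show that medication played no part.

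**The case against.** The case on the other side has several parts.

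- **Only a condensed article is at hand.** The covariates are unnamed, and a fuller plan might deal with medication. It is therefore wrong to infer that no handling exists anywhere. But the article does assign medication a place, description only, and does name its sensitivity analysis. Nor would naming a covariate settle the matter: post-operative medication is a consequence of post-operative pressure, so simple adjustment for it does not recover the effect of surgery.
- **Drugs are not changed at will.** A reader might infer free alteration. The text says regular therapy continues and is adjusted where necessary. That stands. No criteria bound the adjustments, however, so their extent is unknown.
- **Change under usual drug management is a legitimate question**, and medication is a pre-specified endpoint recorded at each relevant visit. This also stands. It would be too strong to say that the primary contrast is uninformative. The gap is that the plan does not say this is the question and does not link the two outcomes, while its aim is attribution to surgery.
- **The size is soft.** The sample size section does not say that 11 mm Hg is a fall at constant medication, the 40% has no time point, and b is assumed. All true; the tables are illustrations.
- **The limitations are openly non-exhaustive.** Also true, but drug change is among the most foreseeable threats and is not named.

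**Conclusion.** The point holds as a should-fix. As written, the primary contrast combines surgery with drug changes that respond to the outcome, and no medication-related sensitivity analysis is stated for it. The direction of each bias follows from the design; the size rests on the assumptions in Step 2.

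Two stronger readings are not supported. One is that power must fall well below the stated 90%. It stays above 90% in three of the six reduction scenarios and is 85% in two more; only 40% reducing at 10 mm Hg each brings it to 60%. The other is that intensification will produce a false positive. With 20% intensified at 10 mm Hg, rejection is 3.9% against 1%: inflated, but far from certain. Nor does the earlier series show that 40% will have stopped drugs by 1 or 3 months.

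**What to change.** Leave the clinical rule on medication as it is and change the analysis.

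1. State how drug changes enter the primary estimand: change under usual drug management, or change at the regimen in force at the 2nd ABPM.
2. Using the medication recorded at the pre-operation, 1-month and 3-month visits, classify each post-operative visit against the 2nd ABPM as reduced, unchanged, increased or substituted.
3. Tabulate systolic ABPM change by that class.
4. Pre-specify one sensitivity analysis of the primary contrast that accounts for drug changes. A tipping-point analysis would do: subtract an assumed drug effect from observed pressure where drugs were reduced, add it where they were increased, try both directions for substitutions, and vary the effect over a range set in advance. A censored-normal model is an alternative, though with about 40 completers it leans on its distributional assumption. Simple covariate adjustment for post-operative medication is not enough.
5. Limit attribution to surgery if the conclusion changes across that range.

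The cost is some wording, modest programming, and an openly stated assumption about drug effect size. No new data are needed. No analysis will fully remove this confounding in an uncontrolled cohort, but this one would show how far the conclusion depends on it.

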### Study endpoints

The primary endpoint is estimated as the difference between systolic ABPM before surgery (2^nd^ measurement) and the systolic ABPM at 1 month and 3 month post-operation (3^rd^ and 4^th^ measurement).

Four secondary endpoints were defined as: 1) The difference between diastolic ABPM before surgery and ABPM diastolic blood pressure at 1 month and 3 month post-operation; 2) control status of blood pressure at 1 month and 3 month post-operation (blood pressure control is achieved if systolic/diastolic blood pressure <140/90 mm Hg, reducing systolic blood pressure by >20 mm Hg or reducing diastolic blood pressure >5 mm Hg); 3) the use and dose adjustment of antihypertensive medication; and 4) the incidence of operative complications, including spinal nerve trauma, incision infection and fluid, pneumonia and urinary system infection etc.

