### Sample size calculation

Based on previous study which explored the efficacy of renal sympathetic denervation in treating hypertension, we assume that for the current study the primary outcome (the change of 24 h ABPM systolic blood pressure from pre-operation to the measurement at 3 months post-operation) has a standard deviation of 15 mm Hg [14]. We wish to be able to detect a difference of 11 mm Hg. Assuming a 20 % drop-out rate, a total of 50 participants are required to provide 90 % power, with the risk of two-sided type І error of 0.01.

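### The primary endpoint covers two post-operative visits in the endpoint and analysis sections but only the 3-month visit in the sample size, so the document does not fix which result decides the study at 0.01

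*Protocol article*

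**What the plan says.** Four places in the protocol article describe the primary comparison.

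- **Study endpoints.** The primary endpoint is the difference between the 2nd systolic ABPM (before surgery) and "the systolic ABPM at 1 month and 3 month post-operation", identified there as the 3rd and 4th measurements.
- **Statistical analysis.** "the primary analysis will be the comparison of systolic ABPM between the 2"nd measurement and the 3rd and 4th. The method is given in general terms: the primary analyses "will be carried out using analysis of covariance, as well as the first secondary endpoint".
- **Abstract, Methods/Design.** The same comparison of the 2nd measurement with the 3rd and 4th.
- **Sample size calculation.** The primary outcome is "the change of 24 h ABPM systolic blood pressure from pre-operation to the measurement at 3 months post-operation". The SD of 15 mm Hg is attached to this change. The section then gives a difference to detect of 11 mm Hg, 20% drop-out, 90% power and a two-sided type I error of 0.01, for 50 participants.

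None of the four says whether success rests on one visit, either visit, both visits or their average.

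**The concern.** Three places name two post-operative readings as primary, and the one that sets alpha and power names a single reading. These are different primary endpoints under one label. At least four decision rules fit the wording: 3 months alone, either visit, both visits, or an average of the two. They do not share the same error rate, and they need not give the same answer on the same data.

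The sponsor chose a strict alpha of 0.01. If the rule can be settled after the data are seen, nothing in the text holds the study to that level. A fall seen only at 1 month could be presented as meeting the endpoint in the Study endpoints section even though the outcome that was sized had failed. This is a single cohort without a control group, and the Discussion concedes that placebo and Hawthorne effects cannot be ruled out. A primary comparison fixed in advance is one of the few safeguards such a design has.

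**Working it through.** **Inputs from the Sample size calculation:** difference 11 mm Hg, SD of the change 15 mm Hg, two-sided alpha 0.01, power 90%, drop-out 20%, total 50. Evaluable patients: 50 × (1 − 0.20) = 40.

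**Assumptions, because the document gives no figure:** the correlation r between the 1-month and 3-month changes, shown from 0 to 0.9; and an effect and SD at 1 month equal to those at 3 months (11 and 15 mm Hg).

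**Step 1. The plan's own figure.** For one mean change, n = (SD × (z for 0.995 + z for 0.90) / difference)² = (15 × (2.576 + 1.282) / 11)² = 27.7, so 28 evaluable and 28 / 0.80 = 35 enrolled. The exact t calculation gives 32 evaluable and 32 / 0.80 = 40 enrolled. The stated 50 is not reproduced, but it exceeds what its inputs require. That is a separate matter; here it means only that there is power to spare.

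**Step 2. Type I error if success at either visit counts.** Error = 1 − P(|Z1| ≤ 2.576 and |Z2| ≤ 2.576), with Z1 and Z2 bivariate normal with correlation r. At r = 0 this is 1 − 0.99² = 0.0199.

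| r | Family-wise error |
|---|---|
| 0 | 0.0199 |
| 0.5 | 0.0190 |
| 0.7 | 0.0177 |
| 0.8 | 0.0166 |
| 0.9 | 0.0149 |

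**Step 3. Type I error under the other rules.**

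- 3 months alone: one test, 0.01.
- Both visits required: at most 0.01, because the visit with no effect must itself be significant at 0.01.
- Average of the two visits: one test, 0.01.
- Either visit, each tested at 0.005: at most 0.005 + 0.005 = 0.01.

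**Step 4. Power with 40 evaluable patients (t-tests).**

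- 3 months alone at 0.01: noncentrality 11/15 × √40 = 4.64, power 96.9%.
- Both required at 0.01: about 94% at r = 0, rising to about 95% at r = 0.8 (simulated).
- Average at 0.01: the SD of the average is 15 × √((1 + r)/2). At r = 0.8 this is 14.2 mm Hg with power 98.2%; at r = 0.9 it is 14.6 mm Hg with power 97.6%. Power is higher at smaller r.
- 0.005 at each visit: 94.4% per visit. For 90% power this needs 36 evaluable, or 36 / 0.80 = 45 enrolled.

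All exceed the stated 90%, so 50 participants suffice under every rule on these assumptions.

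**The case against.** The strongest reply is that the Statistical analysis section describes one before-and-after comparison by analysis of covariance, which can be read as a single pooled or joint test. No sentence says that significance at either visit counts as success. Testing order and alpha splitting are also commonly left to an analysis plan, which is not shown. All of this stands, and it limits the point. A reader might infer that the study's type I error is nearly doubled; the documents do not support that, because the inflation arises under only one of the possible rules. The absence of a multiplicity rule from an article is not, by itself, a fault.

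Two other inferences also fail. A reader might conclude that the study is underpowered for two visits, but power stays above 90% under every rule examined. A reader might also argue that the 1-month reading is likely to show a transient post-operative fall, but nothing in the article says so.

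It can also be said that three of the four places name both visits, so that the sample size wording is the outlier. That is fair, and it means that keeping both visits is a legitimate repair.

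The disagreement over which outcome is primary survives all of this. It lies in the text itself, and a separate analysis plan could not remove it without contradicting one section or the other.

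**Conclusion.** The point holds as an internal contradiction over the primary endpoint. Its consequence is that the stated 0.01 is not guaranteed, not that it is known to be exceeded. The worst case is a family-wise error of 0.0199, or 0.0149 if the two changes correlate at 0.9, and it applies only if either visit may decide. The other three rules in the working hold 0.01, as does splitting alpha between the visits. The correlation range is an assumption. The finding that power is adequate rests on an equal effect and SD at 1 month, which the document does not give. What is at stake is a decision rule that could be chosen after the data are seen, not the number of patients.

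**What to change.** In the Abstract, Study endpoints and Statistical analysis, name the 3-month change (4th minus 2nd systolic ABPM), tested two-sided at 0.01, as the single primary endpoint. This matches the only change the study was sized on. Make the 1-month change (3rd minus 2nd) secondary, either tested only if the 3-month test succeeds or reported as an estimate with its confidence interval.

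If the sponsor prefers to keep both visits as primary, state one rule (both required at 0.01, the average at 0.01, or 0.005 at each visit) and reword the Sample size calculation to match. On the assumptions above, 50 participants cover each of these.

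No extra patients, visits or measurements are needed. Under the single-endpoint option, a fall seen only at 1 month could no longer be called a primary success. The article reports 18 patients already enrolled, so whichever rule is chosen must be recorded as a dated amendment and not treated as an editorial correction.
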